#### Treatment adherence and fidelity assessment

Adherence to treatment was defined by measuring the received therapy dose through number of sessions attended. In the current trial, a completer of treatment was defined as participation in at least five out of eight sessions.

Group leaders digitally recorded all treatment sessions, and recordings were sent to independent evaluators not affiliated with the university or part of the research team. MBCT adherence and competency was provided by an expert in MBCT who reviewed 3 randomly selected sessions from each treatment cohort. For the control condition, external monitoring of treatment HEP adherence and facilitator competency was completed by a HEP expert who also reviewed 3 randomly selected sessions from each treatment cohort. Internal treatment adherence and competency for both interventions was assessed by the principal investigator who reviewed the same 3 randomly selected sessions. The MBCT Adherence Scale [57], an instrument used in the original studies of MBCT, was used to assess treatment fidelity. Inter-rater reliability ranges from 0.59 for the Cognitive Therapy subscale and .97 for the Mindfulness subscale, and 0.82 for global ratings. Competence in delivering MBCT is rated with a newly developed measure, MBCT Competence Scale [13]. This 10-item instrument uses a scale from 0–5 to assess each facilitator’s skill in delivering the treatment. Treatment Fidelity in HEP was assessed using the HEP Adherence Scale. The HEP Adherence Scale is a newly developed scale and is modeled after the MBCT Adherence Scale. It is a 17-item instrument where items are score from 1 to 3. Competence in delivering HEP was rated with a newly developed instrument, the HEP Competency Scale. This is a 10-point scale for rating group facilitator skill and expertise in delivering the intervention. Because the HEP Adherence Scale, HEP Competency Scale, and MBCT Competency Scale have not been previously validated, they will serve as templates for assessment in this study and pilot data for future research. Based on reviews and results of adherence and competency measures, feedback was provided to group leaders during weekly supervision meetings.

### Data safety and monitoring plan

In consultation with NCCAM, an independent Data Safety Monitoring Board (DSMB) was established to oversee all study activities to ensure the safety of participants, the validity of our findings and the need for further data collection. Three categories of patient safety concerns were highlighted for this study: 1) increased depression severity; 2) risk to safety through self-harm and increased suicidal ideation and; 3) study withdrawals that were potentially or definitely related to specific factors in each treatment intervention. Regarding suicidal ideation among enrolled participants, when patients responded positively to the suicidality questions on the HAM-D and QIDS or experienced a 1 or greater point increase from their baseline scores, RAs initiated the following actions they: 1) they notified the PI; 2) provided patients with referrals to crisis hotlines; 3) discussed with patients whether the patient had notified their prescribing physician or mental health provider about their symptoms and; 4) in some cases, where the PI deemed that more clinical contact was warranted, they corresponded via telephone and/or sent confidential letters and email correspondences to providers notifying them of their clinical impressions.

### Planned analytic approach

The primary outcome measure of the HAM-D will be compared between participants randomized to the MBCT + TAU and the HEP + TAU groups using a mixed-effects statistical model [58,59]. Mean levels of severity, and response and remission rates at week 8 and bivariate measures will be compared between treatment conditions using logistic regression models with generalized estimating equations to correct for interdependence resulting from group membership. The secondary outcome measures of the QIDS-SR and CGI will be compared using the same methodology but replacing the HAM-D with the QIDS-SR and CGI severity measures. We will also assess relapse occurrence in both arms using the LIFE interview at weeks 24, 36 and 52.

The efficacy of MBCT + TAU versus HEP + TAU on functional status as a secondary outcome will be assessed using similar models to the methods used to test the reduction in HAM-D_17_ scores. For each of the four scales, scores at week 8 will be compared between randomized conditions using a mixed-effects statistical model, which will include effects for randomized condition, therapy group and baseline disability score. The test of the estimated parameter for treatment condition will be a direct test of this hypothesis. Mediating effects of the relationship of treatment assignment with outcome will be tested using a series of linear regression models. Putative mediators, enhanced mindfulness (FFMQ), enhanced self-compassion (SCS), diminished rumination (RRS) and decreased experiential avoidance (AAQ) will be assessed at weeks 4, 8, 24, 36, and 52. We will also assess persistence of treatment changes in depression (HAM-D, QIDS-SR, CGI), functional status (SF-12, WSAS, Q-LES-Q-SF), mindfulness (FFMQ), rumination (RRS), self-compassion (SCS) and avoidance (AAQ) at weeks 24, 36 and 52 by analyses parallel to those outlined for testing Hypotheses 1 and 2 using data from the weeks 24, 36, and Week 52. Mixed-effects and logistic regression models using a generalized estimating equation (GEE) will allow direct testing of these effects. Moderating factors (e.g. age of depression onset, prior poor treatment outcomes, co-morbid psychiatric diagnoses and other socio-demographics) associated with TRD will also be included in the model.

Additional secondary analyses will test for effects of time. These models will also include indicator variables of any additional treatments (e.g. HEP participants’ crossing over to take MBCT outside of the research), medication changes after the end of acute treatment before the 24, 36 and 52-week follow-ups and also whether or not patients began new psychotherapeutic interventions after treatment or continued formal meditation practices.

Based on the extent and nature of missing data (outcomes, predictors, baseline, and items from scales), we will use one of several strategies for data analysis. We anticipate that the majority of missing data will result from participant attrition. In this case, we will know the randomization assignment and have data from some, but not all, of the planned assessments. Our primary approach to dealing with this monotone missing data pattern will be a pattern-mixture modeling approach [60]. We may also be missing some data on predictors, even in the absence of participant attrition. Our primary method for dealing with missing predictor values will be multiple imputation using a regression modeling approach [60]. This method is superior to simpler methods such as using group means for missing data. In order to limit attrition, we will provide an incentive in the form of an assessment payment schedule to increase motivation to complete all assessments.

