### Description of interventions

The two treatments, MBCT and HEP consisted of 8 weekly classes, each lasting 2.25 hours. In addition to attending weekly classes, participants in both groups were encouraged to complete 45 minutes of homework six days per week for the duration of the 8-week treatments. Both interventions were conducted in a group format with 6–12 participants per group and were led by two facilitators extensively trained in their respective techniques.

MBCT is a manualized treatment that combines training in mindfulness meditation with elements of cognitive therapy. For the purpose of this study, MBCT was adapted from the original manual developed by Segal et al. [11] with modifications for TRD, the details of which are published elsewhere [13]. These modifications are believed to promote enhanced emotional regulation specific to TRD through increasing an individual’s nonjudgmental awareness of their present moment experience [13]. MBCT teaches skills that encourage patients to disengage from habitual (“automatic”) dysfunctional cognitive routines, in particular depression-related ruminative thought patterns, as a way to reduce current symptoms, future risk of relapse and recurrence [16]. Through guided meditation practices and activities, participants are taught to develop more present-focused, non-judgmental awareness of their thoughts and feelings instead of focusing on the content of them [11,14,15,18]. It is theorized that the same cognitive processes known to make individuals prone to depression relapse are also active in perpetuating depression once it is established [12] and are a primary driver of TRD.

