### Sample size

To estimate sample size, effect sizes were based on outcomes from previous studies and our pilot data [15,21-24]. In a review of 21 mindfulness-meditation interventions, Baer [23] found an average effect size of .90 for depressive symptom reduction. In examining the relapse rates of individuals receiving MBCT versus TAU, Teasdale et al. [14] found an effect size of .59 and Ma et al. [15] of .88 for participants with a history of 3 or more depressive episodes. Our pilot data indicated an average effect size of 1.13, which compared similarly to Kenny’s effect size of 1.03 in a TRD population [12]. Finucane et al., working with a more severely depressed population, found an effect size of 1.54 [25]. Kingston et al. found an effect size of 1.07 in reducing depression in psychiatric outpatients [26]. There were no significant differences in effect on depression in a comparison of HEP and MBSR [19,20]. Using the formula provided by Donner and Klar [27], we estimated sample sizes to detect response to the intervention (MBCT + TAU would be superior to HEP + TAU on depression outcomes). Results indicated sample sizes ranging up to approximately 50 per condition. A total sample of 124 participants were regarded as necessary to provide 80% power to detect a moderate effect size in the face with an estimated attrition of approximately 20%, similar to our rates of attrition in clinical MBCT groups.

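### With about 12–20 therapy groups, ordinary GEE would test week-8 response and remission at about 7–10% rather than 5%; a small-sample correction should be named

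*Protocol article*

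**What the plan says.** The Planned analytic approach section of the protocol article compares week-8 response and remission by logistic regression with "generalized estimating equations to correct for interdependence resulting from group membership". The section on primary and secondary outcome measures makes both part of the primary outcome, beside the change in HAM-D score. The same methodology is carried to the QIDS-SR and CGI, and GEE is used again for weeks 24, 36 and 52.

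For the functional scales the article plans a mixed-effects model that "will include effects for randomized condition, therapy group and baseline disability score", and treats the parameter for condition as the test of the hypothesis.

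The number of therapy groups is not given. Description of interventions says: "Both interventions were conducted in a group format with 6–12 participants per group". Sample size says: "A total sample of 124 participants were regarded as necessary to provide 80% power to detect a moderate effect size". Patients are randomised individually, and each therapy group delivers one intervention, so groups are nested in arm.

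The article does not state the working correlation, the variance estimator, the reference distribution or the degrees of freedom for GEE.

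**The concern.** GEE's robust variance is justified when the number of clusters is large. Here the clusters are therapy groups, and there are few of them however many patients are enrolled. With few clusters the uncorrected sandwich variance is biased downwards, and a normal reference ignores that it is itself poorly estimated. Both faults push the same way: intervals too narrow and p-values too small.

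What is at stake is a false claim that MBCT is superior to HEP on two of the primary-outcome measures. The adjustment chosen to deal with clustering would, in its ordinary form, introduce an error of its own.

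**Working it through.** **Inputs from the article.** Total 124; about 50 per condition before attrition; attrition about 20%; 6–12 participants per group.

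**Assumptions not in the article.** Equal allocation (62 per arm); two-sided 5% level; event rates 0.20–0.35; intraclass correlation (ICC) 0–0.05.

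**Step 1: the plan's own total.** The article reports "Results indicated sample sizes ranging up to approximately 50 per condition". Two arms of 50 give 100, and 100 / (1 − 0.20) = 125, against the stated 124. So 124 is reproduced to within one participant, with 124 × 0.80 ≈ 99 evaluable, about 50 per arm.

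**Step 2: number of groups.** Per arm, 62 / 12 = 5.2, so at least 6 groups; 62 / 6 = 10.3, so at most 10. That is 12 to 20 groups in total. Ten groups in total would hold at most 10 × 12 = 120, fewer than 124.

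**Step 3: why the ordinary form fails.** For a treatment-only logistic model with an independence working correlation, the sandwich variance of the log odds in one arm is

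Σ(y_g − n_g p̂)² / [N p̂(1 − p̂)]²,

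summed over that arm's m groups. Because p̂ comes from the same groups, with equal sizes the sum is on average (m − 1)/m of what it should be. An approximate hand check treats the rescaled statistic as t on 2m − 2 degrees of freedom:

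- m = 6: 1.96 × √(5/6) = 1.79, and 2P(t₁₀ > 1.79) ≈ 0.104.
- m = 10: 1.96 × √(9/10) = 1.86, and 2P(t₁₈ > 1.86) ≈ 0.079.

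**Step 4: simulation under no effect.** Beta-binomial outcomes within therapy groups, near-equal group sizes, 50 or 62 per arm, 40,000 replicates per scenario. Ranges are over the event rates and ICCs above.

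| Groups in total | Uncorrected sandwich, z test |
|---|---|
| 12 | 9.4–10.0% |
| 14 | 8.5–9.0% |
| 16 | 7.6–8.5% |
| 18 | 7.2–7.9% |
| 20 | 6.7–7.5% |

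The rates barely move with the ICC and are present at ICC 0. With Kauermann-Carroll variance and t on (groups − 2) degrees of freedom, the error is about 4–5% throughout. A separate rerun of the simulation gave the same picture.

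**Step 5: uneven groups.** Exchangeable GEE, groups of 6–12 with 20% random loss, event rate 0.30, ICC 0.02, 4,000 replicates: 10.4% (12 groups), 9.8% (14) and 9.3% (16). Replacing z by t alone still leaves 6.9%, 6.7% and 7.1%, so the variance correction is needed as well. Mancl-DeRouen variance with t gives 3.2%, 3.1% and 3.6%, which is conservative.

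**Step 6: ignoring clustering is not a remedy.** An unadjusted test at ICC 0.05 with 12 groups and 50 per arm rejects 8.3–9.0% of the time.

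**The case against.** The strongest objection is that the error rate is conditional. The article excludes no correction. The choice of sandwich variant and reference distribution is commonly left to a statistical analysis plan, and that plan is not shown. A reader might infer that no small-sample correction is planned and that the tests therefore run at an inflated level. The article does not support this, because it is silent. This part of the objection stands, and it limits the point to what the named method does in its ordinary form.

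Three further inferences are tempting and also fail.

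- **An error as high as 11%.** With near-equal groups this needs 10 groups in total, which cannot hold 124 participants at 12 per group.
- **A treatment parameter that cannot be estimated.** If therapy group were a fixed effect, it would be collinear with condition, since each group sits in one arm. But the sentence describes a mixed-effects model. With one week-8 score per participant, therapy group is the only listed term that can sensibly be random. The text already points to a random effect and only needs to say so.
- **A linear-model error of 6.6–8.6%.** This is only 2P(t > 1.96) at 18 and 8 degrees of freedom, a ceiling rather than a result for the planned model; 8 degrees of freedom also presupposes 10 groups. A simulated balanced random-intercept model with a normal reference, about 50 per arm and ICC 0.02–0.05, gave 5.1–6.2% with 6 groups per arm and 4.9–5.5% with 10.

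What the objection does not remove is that the article itself fixes GEE on therapy group for primary-outcome measures. At the cluster count its own figures imply, that method in its usual form is miscalibrated.

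**Conclusion.** The concern holds in conditional form. With about 12–20 therapy groups, GEE with an uncorrected sandwich variance and a normal reference would test response and remission at about 7–10% instead of 5%. The result rests on equal allocation, the stated group sizes, and the assumed event rates and ICCs, to which it is insensitive. It is not a statement about the error rate of the plan as documented. For the mixed models there is no demonstrated error, only wording worth making explicit. The point deserves action because it touches primary-outcome measures and the remedy is specific.

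**What to change.** For every GEE analysis clustered on therapy group, specify a bias-corrected sandwich variance (Kauermann-Carroll or an equivalent) and a t reference with degrees of freedom equal to the number of therapy groups minus 2. Keep the adjustment for clustering.

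For the mixed models, state that therapy group is a random intercept nested in arm, with small-sample degrees of freedom such as Kenward-Roger.

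The cost is a sentence or two, standard software options and no new data. Intervals become wider. With equal groups the ratio to the default width on the log-odds scale is (t quantile / 1.96) × √(m/(m − 1)): (2.228 / 1.96) × √(6/5) ≈ 1.25 with 12 groups and (2.101 / 1.96) × √(10/9) ≈ 1.13 with 20. That comparison is with intervals that were too narrow to begin with.

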### Eligibility criteria (inclusion and exclusion criteria)

Participants age 18 or older were required to meet DSM-IV criteria for major depressive disorder and have a total score of 14 or higher on the clinician-rated, 17-item version of the Hamilton Depression Severity Rating Scale (HAM-D) [28] to be eligible for the study. To meet criteria for TRD, participants were required to be taking antidepressant medications with evidence of at least two adequate antidepressant trials prescribed during the current depressive episode. Participants were excluded (Table 3) from the study for the following reasons: they a) met DSM-IV criteria for bipolar disorder, obsessive compulsive disorder, or post-traumatic stress disorder (other comorbid Axis I conditions were noted but not cause for exclusion); b) had a history of schizophrenia or other psychotic symptoms; c) were imminently suicidal, a danger to others or were currently exhibiting self-injurious behavior; d) met DSM-IV criteria for alcohol or substance abuse or dependence within 3 months of study entry; e) were currently practicing meditation more than once per week or yoga more than two times per week; f) had cognitive impairment as evidenced by a score of < 25 on the MMSE; g) were in concurrent individual or group psychotherapy and were not willing to discontinue treatment for the 8-week duration of study treatment; h) had significant or unstable medical illness that would limit participation in HEP; or i) did not have adequate English language comprehension.

**Table 3 T3:** Eligibility criteria for the PATH-D study

**Inclusion criteria**	**Exclusion criteria**
- Age 18 or older	- Clinically significant suicide risk
- Current major depression (DSM-IV-TR criteria)	- History of schizophrenia or psychotic symptoms
- HAM-D total score ≥ 14	- Bipolar disorder
- Total ATHF Intensity score ≥5 for 2 or more antidepressant medications	- Obsessive compulsive disorder
- Evidence of two failed adequate antidepressant trials in the current depressive episode	- Alcohol or substance abuse or dependence within the past 3 months
- Current use of antidepressants	- Insufficient ability to understand or read English
	- MMSE total score < 25
	- Severe medical illness determined by the CIRS
	- History of meditation practice or currently meditation more than 1 time per week
	- Currently practicing yoga more than 2 times per week

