### Randomization and baseline assessment

The unit of randomization was the patient, and randomization tables were stratified by gender to ensure balanced assignment. Patients were randomized during the baseline assessment, which occurred within two weeks of the commencement of treatment (see Figure 1. Study Design and Participant Flow). Baseline assessments served two purposes: 1) to ensure that patients continued to meet eligibility criteria for MDD with scores ≥ 14 on the HAM-D and 2) to serve as the primary data collection point (see Outcome Measures section). Patients who reported improved depressive symptoms during the baseline interview with HAMD total scores < 14, were not randomized to treatment and told that they could be reassessed for a future intervention cohort should their depression symptoms relapse. Participants who continued to be eligible on measures of depressive severity were then randomly assigned to either MBCT + TAU or HEP + TAU.

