### Primary and secondary outcome measures

The primary outcome measurement was improvement of depression severity after 8 weeks, as measured through change in HAM-D total scores from pre- to post-treatment, treatment response (scores ≥ 50% decrease from baseline) and remission (post-treatment scores ≤ 7). Length of treatment efficacy, a secondary outcome, was assessed up to 1 year after baseline using HAM-D scores, response and remission rates by measuring rate of depression relapse using the semi-structured Longitudinal Interval Follow-up Evaluation (LIFE) [35]. The participant-rated 16-item Quick Inventory of Depressive Symptomatology (QIDS) [36] was used as a secondary measurement to assess change in depressive severity, response (scores ≥ 50% decrease from baseline) and remission (scores ≤ 5) during the same treatment and follow-up time period.

Functional status and quality of life were additional secondary outcomes measured using the SF-12 Health Survey [37,38], the Work and Social Adjustment Scale (WSAS) [39], [40] and the Quality of Life, Enjoyment, and Satisfaction Questionnaire (Q-LES-SQ) [41].

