## Discussion

Treatment-resistant depression is a condition associated with high rates of disability, chronicity, reoccurrence and failed response to antidepressant treatment [3,8]. Through decreased workforce productivity and disability, the economic burden caused by refractory depression is enormous [10,61]; hence the importance of finding effective treatment modalities for this population is clear and of vital public health interest. This investigation represents the first RCT to evaluate MBCT for TRD. Results from this study will address whether MBCT is superior in reducing depression severity after 8 week treatment and improving relapse and remission rates over time in comparison to a credible comparator condition, developed to control for non-specific treatment effects. If successful, this study will identify an augmentation treatment for a large, hard-to-treat population for whom few treatments have been effective.

After analysis, we will be able to assess whether the specific constructs of a mindfulness-based intervention, such as the putative mediators in MBCT (increased mindfulness, self-compassion and decreased rumination and experiential avoidance) are enhanced more after an 8-week treatment with MBCT compared with HEP, and whether they are associated with positive treatment outcomes. We will also be able to evaluate whether treatment gains between groups (i.e. reduced depression severity, increased functional status) are retained during a 1-year follow-up and whether differential effects might be mediated by the specific constructs of MBCT listed above. Finally, we will be able to assess whether participant expectancy, treatment adherence (i.e. number of sessions attended), and compliance (i.e. number of minutes of homework completed) predicted treatment outcomes.

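### Everyone is randomised while depressed, so the LIFE relapse rate cannot support a between-arm superiority claim on relapse

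*Protocol article*

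**What the plan says.** All participants enter in an active episode. Under Eligibility criteria they were "required to meet DSM-IV criteria for major depressive disorder and have a total score of 14 or higher" on the 17-item HAM-D. The threshold was applied again immediately before allocation (Randomization and baseline assessment): "Patients who reported improved depressive symptoms during the baseline interview with HAMD total scores < 14, were not randomized to treatment".

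Under Primary and secondary outcome measures, the duration of benefit up to one year is a secondary outcome. It is followed with HAM-D scores, response and remission, and "by measuring rate of depression relapse using the semi-structured Longitudinal Interval Follow-up Evaluation". The Planned analytic approach adds: "We will also assess relapse occurrence in both arms using the LIFE interview at weeks 24, 36 and 52". According to the Discussion, the results will address whether MBCT is superior in, among other things, "improving relapse and remission rates over time in comparison to a credible comparator condition". The Summary again lists relapse among the outcomes on which MBCT may be more effective than the comparator.

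The article does not state who is at risk of relapse, which denominator applies, when the clock starts, or what remission rate is expected. It does plan analyses of HAM-D, QIDS-SR and CGI at weeks 24, 36 and 52, parallel to the main models. Table 4 schedules LIFE, the SCID mood module and the HAM-D at weeks 8, 24, 36 and 52.

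**The concern.** A relapse rate is a natural outcome when patients are randomised in remission, because everyone is then at risk from time zero. Here nobody is. A participant must first remit, or at least respond, and that is what the interventions are meant to change. Two denominators suggest themselves, and neither gives a sound comparison of the arms.

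- **Those who improved.** Treatment helps decide who enters this group. If one arm also brings harder-to-treat, more relapse-prone patients into remission, its remitters are a less favourable mix, and randomisation no longer protects the comparison.
- **All randomised.** A patient who stays depressed for the whole year counts as not relapsed. The arm that helps fewer people has fewer who can relapse, and so looks better.

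At stake is a stated superiority claim on a secondary outcome. The relapse result could point against the arm that gives more patients a lasting remission.

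**Working it through.** **Sample size.** The Sample size section gives about 50 per condition, about 20% attrition and 124 in total. 50 / 0.80 = 62.5 per arm, or 125 in total, which agrees with 124 to within rounding. With 1:1 allocation that is 62 randomised and 62 × 0.80 = 49.6, about 50, evaluable per arm.

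**Number of remitters (assumed rates).** No remission rate is planned for this trial. The only benchmark, in the Background, is 30% after a first antidepressant trial and lower after later ones. I therefore take 10 to 30%.

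| Assumed remission | Of 50 evaluable | Of 62 randomised |
|---|---|---|
| 10% | 5.0 | 6.2 |
| 20% | 10.0 | 12.4 |
| 30% | 15.0 | 18.6 |

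The range is about 5 to 19 per arm.

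**Precision among remitters.** The 95% half-width for a difference in relapse rates is 1.96 × √(2p(1−p)/n). With p of 0.4 or 0.6, p(1−p) = 0.24:

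- n = 5: 1.96 × √(0.48/5) = 0.61
- n = 12.4: 1.96 × √(0.48/12.4) = 0.39
- n = 18.6: 1.96 × √(0.48/18.6) = 0.31

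The half-width is thus roughly 30 to 60 percentage points. At a relapse rate of 20% (p(1−p) = 0.16) the same formula gives 50 points at n = 5 and 26 at n = 18.6. Power to detect a fall in relapse from 60% to 30% (two-sided 5%, normal approximation) is about 17% with 6 remitters per arm, 31% with 12 and 48% with 20.

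**Direction of the bias (assumed rates).** Let remission be 20% on HEP and 30% on MBCT. Treat the MBCT remitters as 20% who would remit on either programme plus 10% who remit only on MBCT.

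*Case A: equal relapse of 40% in all remitters.*

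- Among remitters: 40% v 40%.
- Per randomised: 0.20 × 0.40 = 8% v 0.30 × 0.40 = 12%.
- Sustained remission: 20 − 8 = 12% v 30 − 12 = 18%.

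*Case B: relapse of 30% in those who would remit on either, 60% in the extra MBCT remitters.*

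- Among remitters: 30% v (0.20 × 0.30 + 0.10 × 0.60)/0.30 = 0.12/0.30 = 40%.
- Per randomised: 6% v 12%.
- Sustained remission: 20 − 6 = 14% v 30 − 12 = 18%.

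The rate per randomised participant favours HEP in both cases, and sustained remission favours MBCT in both. The rate among remitters reverses only in Case B.

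**How much direct relapse prevention would undo the reversal?** Suppose MBCT also lowered relapse among its remitters directly.

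- Case B, among remitters: the reversal disappears once relapse falls by 1 − 30/40 = 25%.
- Per randomised: it disappears only once relapse falls by 1 − 8/12 = 33% (Case A) or 1 − 6/12 = 50% (Case B).

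**The case against.** The strongest reply is that the article commits to very little. It says relapse will be assessed in both arms, which could mean descriptive reporting. It names no test, denominator or restriction to remitters, and a condensed article may leave these to the full protocol or analysis plan. That stands: an unstated denominator is no finding here. But the point does not depend on the omission. Both natural denominators fail as an arm comparison, and the Discussion and Summary do announce a comparative conclusion.

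Second, durability does not rest on relapse alone. HAM-D, response and remission are followed to week 52, and the HAM-D, QIDS-SR and CGI analyses then use models parallel to the main ones. This also stands, and it limits the point to the relapse component.

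Third, the reversal among remitters needs two assumptions: that the additional remitters are more relapse-prone, and that MBCT has little direct effect on relapse. The Abstract describes MBCT as effective for relapse prevention, so the second is open to doubt. In Case B a 25% direct reduction removes the reversal. This stands for that denominator. The reversal per randomised participant is more robust, since Case A produces it with no difference in relapse-proneness at all.

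A reader might also infer that the plan compares a fixed group of about a dozen remitters per arm. The article supports neither the restriction nor the number. Twelve is simply 20% of 62 or about 24% of 50. If responders also count as at risk, the set is larger, though still selected by treatment.

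**Conclusion.** The point holds as a limited one about a secondary outcome. With every participant randomised in a current episode, the LIFE relapse rate cannot support the between-arm superiority claim in the Discussion and Summary, and it can point against the arm that brings more patients into remission. That rests on the entry criteria alone. The sizes rest on assumptions: remission of 10 to 30%, and relapse near 40 or 60% for the half-width of roughly 30 to 60 points. The reversal per randomised participant is robust in the cases shown; the one among remitters is conditional.

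A reader might infer that the trial's whole assessment of durability is compromised, or that MBCT is bound to look worse on relapse. The documents support neither. The week-8 primary analysis and the planned persistence analyses of HAM-D, QIDS-SR and CGI to week 52 are unaffected, and the direction of the relapse result depends on unknown rates.

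**What to change.** - Base the comparative durability claim on an outcome defined for everyone randomised and analysed by assigned arm. One choice is sustained remission: remitted at week 8 and no relapse on LIFE through week 52. Another is weeks well to week 52 from LIFE, which also credits patients who remit after week 8. Present it alongside the HAM-D and remission analyses already planned.
- Report relapse among remitters or responders descriptively, with its denominator, and make no superiority claim from it.
- Reword the Discussion and Summary so that the comparative statement concerns sustained remission, or the course of symptoms, to one year.

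No new data are needed, because Table 4 already schedules LIFE, the SCID mood module and the HAM-D at weeks 8, 24, 36 and 52. The cost is a little extra analysis and a narrower claim about relapse.
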